## Abstract

**Introduction::**

Cardiovascular autonomic dysfunction reflex of the pathophysiology of diabetes mellitus (DM) favors an increase in morbidity and mortality related to cardiovascular events, and for this reason has been one of the most studied clinical entities.

**Method::**

An experimental study of a randomized clinical trial type was therefore proposed to analyze the hemodynamic and glycemic response after the practice of a rehabilitation program in patients with type 2 diabetes mellitus (T2DM). In this clinical trial the patients will initially be submitted to an evaluation protocol that consists of assessing blood pressure, heart rate, Borg scale, respiratory rate, oxygen saturation, distance traveled through the 6-minute walk test, quality of life questionnaire, Pittsburgh sleep quality questionnaire, and still glycated hemoglobin and heart rate variability through the cardiofrequency meter. After careful evaluation of the patients, they will be submitted to a metabolic rehabilitation program composed of aerobic and resisted exercises, performed for 12 weeks, in 3 weekly meetings of 60 minutes each. With such evaluations, it will be possible to construct with evidence that it is possible to work safer metabolic rehabilitation programs in patients with T2DM or other diseases that generate cardiovascular risks, guaranteeing them an improvement in cardiorespiratory fitness, hemodynamic and glycemic variables, allowing improvement of the quality of life.

**Ethics and Dissemination::**

The protocol is approved by the host institution's ethics committee under the number 1.616.721. Results will be disseminated via peer-reviewed journal articles and conferences. This clinical trial is registered at ClinicalTrials.gov identifier: NCT3094767.

## Introduction

1

Chronic noncommunicable diseases are the leading cause of morbidity and mortality in the world. In 2009, in Brazil, they accounted for more than 70% of all deaths, of which 31.3% were related to cardiovascular diseases (CVD). Each year it is estimated that more than 17 million people die from some CVD. Most of the risk factors for these diseases are related to living conditions and are estimated to be responsible for more than 40% of global mortality worldwide (hypertension, smoking, high blood glucose, sedentary lifestyle, overweight, and obesity).^[1]^

CVDs are the main cause of morbidity and mortality in the world.^[2,3]^ They were responsible for more than 17 million deaths in 2008, of which 3 million occurred before the age of 60, and much of it could have been avoided. The World Health Organization estimates that by 2030 almost 23.6 million people will die from cardiovascular disease.^[3,4]^

The set of cardiovascular risk factors result in the metabolic syndrome which is a complex disorder that can lead to the occurrence of CVD. Healthy living habits are strongly related to the improvement of the quality of life and positively interfere in the control of the risk factors present in this clinical condition, minimizing the chances of occurrence of CVD.^[5]^

Among the cardiovascular risk factors is diabetes mellitus (DM), characterized by a heterogeneous group of metabolic disorders resulting from defects in insulin secretion and/or action, leading to hyperglycemia.^[6]^ DM is responsible for high morbidity rates worldwide, including young individuals.^[7,8]^

In the epidemiological narrative review proposed by Petermam,^[9]^ a variation of 2% to 13% of DM in the Brazilian population in the last 3 decades was observed, being more prevalent in women, elderly, sedentary, subjects with lower educational level and those overweight or obese.

According to the International Diabetes Federation,^[8]^ an epidemic of DM is underway, with the number of diabetics worldwide being approximately 382 million, reaching 471 million in 2035.

Among the several complications from DM, neuropathies are included, and autonomic cardiac neuropathy is one of the most worrying, since it is related to the higher risk of developing cardiac diseases and mortality in this population, due to the presence of autonomic nervous system alterations.^[10–12]^

This group of patients presents an increase in morbidity and mortality related to cardiovascular events, and for this reason it has been one of the most important clinical entities.^[10–12]^ Therefore, it is understood that studies on the behavior of blood pressure (BP), and heart rate (HR), as well as the autonomic control of circulation and glycemic control in diabetic individuals, may contribute to the understanding of the pathophysiological mechanisms involved.^[13]^

The study by Lee et al^[14]^ demonstrated that regardless of the type of exercise intervention, this practice is potentially effective in improving the metabolic control of patients with type 2 diabetes mellitus (T2DM).

Therefore, to analyze the hemodynamic and glycemic behavior in relation to the real role of physical exercise in patients with T2DM, as well as all cardiovascular and metabolic diseases, will allow a more in-depth analysis of the heart rate variability (HRV), a technique used to evaluate the Performance of the autonomic nervous system, and of the metabolic markers pertinent to each disease.

The knowledge of these data can be used as a physiological parameter for the prescription of exercises, favoring the search for interventions that early improve not only the metabolic control, but also the autonomic dysfunction, guaranteeing the practice of metabolic rehabilitation programs that favor the activation of the autonomic modulation in a safety way, based on evidence, allowing improvement of their quality of life and reducing the morbidity and mortality rates related to CVD.

## Method

2

This study protocol followed the Items of the Standard Protocol for Randomized Assays (SPIRIT). This is an experimental study of the type randomized clinical trial on the autonomic response and cardiovascular and metabolic serum markers of individuals submitted to a metabolic rehabilitation program.

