### Intervention

2.5

Raimundo et al,^[15]^ used a program based on 5 minutes of warm-up and 25 minutes of aerobic exercise. Such a program was adapted to increase the aerobic exercise time to 30 minutes. Therefore, individuals will be referred to a treadmill where they will begin aerobic exercise, consisting of 5 minutes of warm-up and 30 minutes of aerobic exercise, during which they will be monitored to maintain between 50% and 70% of their HR calculated individually.

After completing the aerobic training, the patients will be able to begin resistance training, which was adapted from the study by Umeda,^[16]^ which will consist of light weight exercises, comprising a load of up to 40% to 60% of that found in the test of a maximum repetition up to 3 sets of 10 repetitions increased by 10 minutes as proposed by Umeda for 20 minutes, followed by 5 minutes of deceleration.

We chose a program of aerobic and resistance exercises based on the results of the study by Church,^[17]^ where they found better results in patients with T2DM that combined aerobic activities and resistance training compared to the control group (without exercise) and also in comparison with the group that trained with aerobic or isolated resistance exercises.

The metabolic rehabilitation program consists of aerobic and anaerobic exercises performed for 12 weeks in 3 weekly meetings of 60 minutes each, totaling 36 sessions, performed in a period of 3 months.

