### Data collection

2.6

The evaluation instrument of the research will be applied before and after the practice of the proposed rehabilitation program. The instrument is based on the following collection protocol: BP, HR, Borg scale, respiratory rate, oxygen saturation, distance walked through the 6-minute walk test (6MWT), quality questionnaire (Which must be specific for each disease, and therefore the research used the diabetes quality of life-Brazil-DQOL), sleep quality questionnaire (Pittsburgh) and also the outcome variables that are glycated hemoglobin (sent by physician along with medical referral) and HRV through the cardiofrequency meter.

It is also suggested the insertion of cardiovascular and metabolic serum markers of individuals submitted to a metabolic rehabilitation program, in order to evaluate patients regarding cardiovascular risks.

With this evaluation, before and after the rehabilitation program, it will be possible to observe the response of these variables (Fig. 1).

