### Primary outcomes

4.1

Recruitment began in September 2016, and is underway. A total of 9 patients were evaluated and submitted to the intervention protocol by the end of June 2017.

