### Data analysis

4.3

Data will be expressed as mean and standard deviation. The SPSS software version 24.0 will be used for statistics. The descriptive data will be measured by measures of central tendency and dispersion. The Shapiro–Wilk test will be used to verify the normality of the data. To compare the cardiorespiratory parameters, we will use the Friedmann test or the ANOVA test of repeated measures according to the normality of the data. The level of significance will be *P* < .05. All values will be compared with the rest condition.

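### The article labels the study a randomized clinical trial but describes one treated group, no randomization and no between-group comparison, so its 12-week change cannot support the causal conclusions it announces

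*Protocol article*

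**What the plan says.** The design label appears twice. The abstract's Method paragraph says: "An experimental study of a randomized clinical trial type was therefore proposed to analyze the hemodynamic and glycemic response". Section 2 (Method) says: "This is an experimental study of the type randomized clinical trial", and adds that the protocol follows SPIRIT.

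The operational text reads as follows:

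- **Flow (abstract, Method):** "After careful evaluation of the patients, they will be submitted to a metabolic rehabilitation program composed of aerobic and resisted exercises".
- **Intervention (2.5):** one regimen is described, introduced with "individuals will be referred to a treadmill where they will begin aerobic exercise". The only control group mentioned in that section belongs to a cited study.
- **Data collection (2.6):** "The evaluation instrument of the research will be applied before and after the practice of the proposed rehabilitation program". The section closes with: "With this evaluation, before and after the rehabilitation program, it will be possible to observe the response of these variables".
- **Progress (4.1, under the heading Primary outcomes):** "A total of 9 patients were evaluated and submitted to the intervention protocol by the end of June 2017".
- **Analysis (4.3):** "we will use the Friedmann test or the ANOVA test of repeated measures according to the normality of the data". The section then states that every value is compared with the rest condition.

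On conclusions, the abstract expects evidence for safer rehabilitation programmes that guarantee improvement in fitness, hemodynamic and glycemic variables. Section 2.4 hopes for much the same.

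**The concern.** Randomization is the property that allows a difference in outcome to be attributed to the treatment. The label claims that property, and the design as described does not have it. This is not a request for the sequence method, the allocation ratio or concealment, all of which a condensed article may leave to the full protocol. The difficulty is that what is stated conflicts with the label.

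The stake is the 12-week effect. Section 2.2 admits sedentary patients on medical referral with a current glycated hemoglobin result. In such patients several things can move the before-after difference without any effect of exercise:

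- regression to the mean, if referral follows a poor value;
- changes in medication over the 12 weeks;
- familiarity with the 6-minute walk test the second time;
- the attention that comes with 36 supervised sessions.

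A claim that programmes become safer also needs something to be safer than. Readers, and anyone pooling evidence, could grade the result as randomized when it is not.

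**Working it through.** The article states no sample size, power or effect figure, so there is no figure of the plan's own to reproduce. The check has two parts.

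**1. Label against description.** I looked in each section on design, flow, intervention, measurement, progress and analysis for three things: a second arm, a randomization step, and a between-group comparison.

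| Place | What it implies |
|---|---|
| Abstract (Method) and section 2 | Randomized trial |
| Abstract (Method), flow | Evaluation leads straight to the programme, with no allocation step between |
| 2.5 Intervention | One regimen; the control group belongs to a cited study |
| 2.6 Data collection | Response is read as before versus after |
| 2.7 Instruments | Exercise heart rate variability is recorded pre- and postintervention, across the stages of a session |
| 4.1 | 9 patients evaluated and treated; no control patients mentioned |
| 4.3 Data analysis | Friedman or repeated-measures ANOVA, with rest as reference |

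Count over the text: arms described, 1; randomization steps described, 0; between-group comparisons named, 0.

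Two contrasts need to be kept apart. The first is the response within a session (warm-up, aerobic, strength and cool-down stages against rest). It is descriptive, uses each patient as their own reference and needs no control arm. The second is the change over the 12-week programme, and the causal objection applies to this one.

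**2. Illustration of the consequence.** Inputs:

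- n = 9, the number reported in section 4.1;
- n = 30, an assumption, because the article gives no target size;
- significance level 0.05, from section 4.3; two-sided is assumed, because the article does not say;
- true programme effect zero, an assumption;
- drift d, the mean change from other causes divided by the SD of the individual change, assumed between 0.1 and 0.5;
- a paired t test, standing in for the methods named in section 4.3.

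Formula: the rejection probability is P(|T| > c), where T is noncentral t with n − 1 degrees of freedom and noncentrality d√n, and c is the 0.975 quantile of the central t.

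- n = 9: c = 2.306 and √n = 3, so d = 0.1 gives noncentrality 0.3 and d = 0.5 gives 1.5.
- n = 30: c = 2.045 and √n = 5.477, so d = 0.1 gives noncentrality 0.548 and d = 0.5 gives 2.739.

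| Drift d | n = 9 | n = 30 (assumed) |
|---|---|---|
| 0.1 | 6% | 8% |
| 0.2 | 8% | 19% |
| 0.3 | 13% | 36% |
| 0.5 | 26% | 75% |

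The nominal rate is 5%. For any fixed drift the false attribution rate rises with n, so further recruitment to the same design does not cure the problem.

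**The case against.** The strongest reply is that this is a condensed article. Figure 1 is not available here and the full protocol is not shown, so a control arm could be described there. That stands as far as it goes. A reader might infer that the trial has no comparator, but the documents support only that the article describes none. The conflict between the label and the text remains, and it needs resolving either way.

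A reader might also infer from section 4.1 that every patient evaluated was treated. The sentence gives no denominator. It reports 9 patients evaluated and treated and does not exclude others. It is consistent with a single arm but does not prove one.

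The analysis section is not conclusive either. Comparison with rest fits the within-session aim, and repeated-measures ANOVA can carry a group factor. The Friedman alternative cannot, and no group factor is named, so the section leans towards one group without settling the matter.

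It can fairly be said that some of the benefit wording is aspirational: section 2.4 is framed as a hope, and the stated aims are to analyse, observe and describe. This softens the point but does not remove it, because the abstract still presents guaranteed improvement and safer programmes as what the evaluations will make possible.

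Finally, the percentages rest on an assumed drift and, for 30 patients, an assumed size. That is correct. At a small drift the inflation is slight, and the finding does not depend on these figures.

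**Conclusion.** The point holds as a contradiction between the design label and the design described. The abstract and section 2 say randomized, while the flow, intervention, measurement and analysis text describe one group followed before and after. It must be corrected, because the label determines what the study can claim.

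The consequence is confined to the 12-week effect. As described, that change cannot be separated from the other causes of change and cannot support the conclusion that the programme improves outcomes or is safer. It would go too far to say that no useful conclusion can be drawn: the within-session heart rate variability response against rest stands as within-patient description.

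The documents give no basis for sizing the bias. The illustrative rejection rates of about 6% to 26% (n = 9) and 8% to 75% (n = 30) show a direction and a range under the stated assumptions, and are not an estimate for this trial. The verdict rests on the article text alone and would change in form, though not in the need for action, if a randomized comparator exists that the article does not mention.

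**What to change.** **If there is one group:**

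- In the abstract and section 2, replace the randomized label with *single-arm, uncontrolled before-after study*.
- Report the 12-week results as within-group changes with 95% confidence intervals.
- In the abstract and section 2.4, remove wording that guarantees improvement, attributes it to the programme or claims safer programmes.
- In section 4.3, state separately which analysis serves the within-session response and which serves the 12-week change.

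**If a randomized comparator exists:** describe the comparator and the allocation, and make a between-group comparison adjusted for baseline the analysis of the 12-week effect.

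**Cost:** in the first case, changes of wording and a weaker claim. In the second, a description of what is already being done and a revised analysis paragraph. Neither route requires new patients or a change in treatment.

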### Study population

2.1

The study population consists of diabetic patients assisted at the Health Institution called Policlínica do Tucumã, located in the municipality of Rio Branco-Acre.

### Inclusion and exclusion criteria

2.2

Included in the research are the T2DM individuals, of both sexes, sedentary, nonsmokers, referred with medical prescription and current glycated hemoglobin result.

Patients with neurological disease, acute heart failure, type 1 diabetes, morbid obesity, atrial fibrillation, sinus arrhythmia, grade II or III atrioventricular block, smokers, and those taking beta-blockers or antiarrhythmic medication were excluded from the study.

### Expected risks

2.3

Some risks related to the study may be: dizziness and small tiredness due to physical exercise, however in the presence of these symptoms, exercise will be interrupted until the patient is stabilized.

### Expected benefits

2.4

It is hoped to make it possible to work cardiovascular rehabilitation programs in patients with T2DM more safely, guaranteeing them an improvement in cardiorespiratory, hemodynamic and glycemic conditioning, allowing them a better quality of life, contributing to scientific advancement.

### Intervention

2.5

Raimundo et al,^[15]^ used a program based on 5 minutes of warm-up and 25 minutes of aerobic exercise. Such a program was adapted to increase the aerobic exercise time to 30 minutes. Therefore, individuals will be referred to a treadmill where they will begin aerobic exercise, consisting of 5 minutes of warm-up and 30 minutes of aerobic exercise, during which they will be monitored to maintain between 50% and 70% of their HR calculated individually.

After completing the aerobic training, the patients will be able to begin resistance training, which was adapted from the study by Umeda,^[16]^ which will consist of light weight exercises, comprising a load of up to 40% to 60% of that found in the test of a maximum repetition up to 3 sets of 10 repetitions increased by 10 minutes as proposed by Umeda for 20 minutes, followed by 5 minutes of deceleration.

We chose a program of aerobic and resistance exercises based on the results of the study by Church,^[17]^ where they found better results in patients with T2DM that combined aerobic activities and resistance training compared to the control group (without exercise) and also in comparison with the group that trained with aerobic or isolated resistance exercises.

The metabolic rehabilitation program consists of aerobic and anaerobic exercises performed for 12 weeks in 3 weekly meetings of 60 minutes each, totaling 36 sessions, performed in a period of 3 months.

### Data collection

2.6

The evaluation instrument of the research will be applied before and after the practice of the proposed rehabilitation program. The instrument is based on the following collection protocol: BP, HR, Borg scale, respiratory rate, oxygen saturation, distance walked through the 6-minute walk test (6MWT), quality questionnaire (Which must be specific for each disease, and therefore the research used the diabetes quality of life-Brazil-DQOL), sleep quality questionnaire (Pittsburgh) and also the outcome variables that are glycated hemoglobin (sent by physician along with medical referral) and HRV through the cardiofrequency meter.

It is also suggested the insertion of cardiovascular and metabolic serum markers of individuals submitted to a metabolic rehabilitation program, in order to evaluate patients regarding cardiovascular risks.

With this evaluation, before and after the rehabilitation program, it will be possible to observe the response of these variables (Fig. 1).

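### Baseline HbA1c is the referral result, with no set interval before session 1, and a referral cannot supply the post-programme value

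*Protocol article*

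**What the plan says.** Section 2.6 (Data collection) refers to "the outcome variables that are glycated hemoglobin" and heart rate variability, and gives the source of the first as "glycated hemoglobin (sent by physician along with medical referral". The same section says "The evaluation instrument of the research will be applied before and after the practice of the proposed rehabilitation program", and that the response of the variables will be read from these two occasions.

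Section 2.2 (Inclusion and exclusion criteria) makes the result an entry requirement: patients are "referred with medical prescription and current glycated hemoglobin result". It gives no maximum age for the result and no HbA1c threshold.

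Section 2.5 (Intervention) describes a programme "performed for 12 weeks in 3 weekly meetings of 60 minutes each, totaling 36 sessions".

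The Method section says "This is an experimental study of the type randomized clinical trial", but no comparator arm is described. Section 4.3 (Data analysis) sets out repeated-measures tests for the cardiorespiratory parameters and ends with "All values will be compared with the rest condition". It describes no between-group contrast. The registered title given in section 5 includes glycated hemoglobin.

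**The concern.** A before-after difference measures the programme only if the first value belongs to its start and the second to its end. Here the first value comes from a clinical document prepared before the study evaluation, and the source of the second is not stated. Three things follow.

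- The time from blood draw to session 1 is not controlled and can differ between patients. HbA1c change in that time, for example after a treatment change or a loss of control, is counted as programme response.
- The stated source fits only one of the two occasions. Each site or assessor would have to decide where the final value comes from.
- A referral result followed by a value from some other source does not ensure the same laboratory and method for both.

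At stake is the reading of one of the two named outcomes. A larger sample does not help, because the average pre-programme change does not shrink as patients are added.

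**Working it through.** The article states no sample size, effect size or standard deviation for HbA1c, so there is no figure to reproduce. The check is a decomposition, a timing illustration and a test of how far regression to the mean can be claimed.

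**1. What the difference contains.** Let H(t) be a patient's HbA1c at week t, with session 1 at week 0, programme end at week 12 (section 2.5) and the referral sample taken L weeks before session 1. Then

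observed difference = [H(12) − H(0)] + [H(0) − H(−L)] + (measurement error and any laboratory difference).

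The first bracket is the change over the programme. The second is change before it began. It vanishes if L = 0 or if HbA1c was stable. Otherwise it can be negative (flattering the programme) or positive (hiding a benefit). The documents fix neither L nor its limit.

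**2. How much of the interval is programme time.** Share = 12 / (12 + L).

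| L (assumed) | Calculation | Share |
|---|---|---|
| 0 weeks | 12 / 12 | 100% |
| 2 months, 8.7 weeks | 12 / 20.7 | 58% |
| 3 months, 13 weeks | 12 / 25 | 48% |

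The share describes timing only. It does not give the size of any bias.

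**3. The post-programme value.** Section 2.6 requires the measurements before and after the programme and names one source for HbA1c. Section 2.2 places that source at entry. No second referral is described, so the source and the schedule in section 2.6 do not fit together for the final value.

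**4. Regression to the mean.** The entry criterion "Included in the research are the T2DM individuals, of both sexes, sedentary, nonsmokers" and the rest of section 2.2 set no HbA1c cut-off, and nothing says that a high value triggers referral. With no selection on HbA1c the expected regression is 0. In a simulation with no true effect (20,000 replicates per setting), a paired t-test at two-sided 0.05 kept about 5% type I error.

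If referral did select values above a cut-off c (in SD units from the mean), the expected fall in SD units for bivariate normal values with correlation ρ would be (1 − ρ) × φ(c) / [1 − Φ(c)].

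| Selection (assumed) | ρ = 0.9 | ρ = 0.8 | ρ = 0.7 | ρ = 0.6 |
|---|---|---|---|---|
| None (all that the documents support) | 0 | 0 | 0 | 0 |
| c = 0 | 0.08 | 0.16 | 0.24 | 0.32 |
| c = +1 SD | 0.15 | 0.31 | 0.46 | 0.61 |

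For example, at c = 0 and ρ = 0.8: 0.2 × 0.3989 / 0.5 = 0.16. Both c and ρ are assumptions. The table shows that the answer depends on a selection rule that the documents do not contain.

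**The case against.** **An article condenses.** Sampling windows and assay details are often left to the full protocol, and Figure 1, which may show timing, is not available. This stands for laboratory and assay taken alone. It does not cover the main point: the article does name a source for HbA1c, and that source is not tied to session 1 and cannot serve the second occasion.

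**The entry criteria ask for a current result.** This is correct, and a reader who calls the baseline undated would go too far. Recency is required; what is missing is a defined window.

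**The study is called randomized.** A randomized between-arm comparison would remove pre-programme drift and regression to the mean in expectation. But no comparator arm or between-group contrast is described, so as written nothing does this. That absence is a separate matter, and the missing source for the final value does not depend on it.

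**All patients attend one polyclinic (section 2.1).** The two values may in practice come from one laboratory. The point is only that the referral route does not ensure it.

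**Bias in favour of the programme.** A reader might infer that patients were referred because their HbA1c was high, and so that a spurious fall must be expected. The documents say that the result accompanies the referral, not that it prompted it. Nor would an old baseline necessarily flatter the programme, since control may have worsened before session 1.

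**Conclusion.** The point holds in this form: the HbA1c baseline is a referral value with no defined interval to session 1, so pre-programme change in either direction is mixed into the before-after difference, and the stated source cannot supply the post-programme value. No comparator arm is described that would remove the pre-programme change.

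Neither the size nor the direction of the bias can be derived from the documents. The 48% to 58% share rests on an assumed sample age of 2 to 3 months. Regression to the mean is a conditional risk, zero under what is stated and above zero only if referral favours high values. It should not be reported as an established bias or given a figure in HbA1c points.

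This should be corrected because it concerns a named outcome and recruitment is still underway. It does not affect heart rate variability or the walk test, which have their own collection procedures.

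**What to change.** For patients who have not yet started the programme:

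- Use the referral HbA1c for eligibility only.
- Obtain the outcome HbA1c at the pre-programme and post-programme evaluations that already exist. Each sample should fall within a stated window of the first and last session (for example 14 days, to be set by the study team).
- Use the same laboratory and method for both, and record the sampling dates.

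Section 4.1 reports 9 patients evaluated and submitted to the intervention by the end of June 2017. For these and any others already treated, no new baseline can be taken. Report the interval from referral sample to session 1 and the source of the final value. Keep these patients in the main analysis, and add a sensitivity analysis excluding those whose baseline falls outside the window.

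The cost is a change of wording and a routine blood test at each evaluation; the final one is needed in any case. The sensitivity analysis will have fewer patients and so less precision.
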